### Statistical analysis

All data analyses will be performed using SPSS Statistics software v21.0 (IBM Corporation, Armonk, NY, USA). All randomized patients will be analyzed, including those who stop receiving treatment, on an intention-to-treat (ITT) as well as treatment-completer basis. The multiple imputation method will be used for missing data when appropriate. Analyses of variance with repeated measures (three measurement points: pre, post, and follow-up) will be applied for continuous data (primary outcomes: STAI, HAM-A, CGI-S, and CGI-I; secondary outcomes: BDI-II, OQ-45, SES, DSQ-40, PBQ, IIP, DWM-S, ECR, BORRTI; MCQ, and SWLS). Primary planned comparison is the interaction between the time (pre-to-post and post-to-follow-up change on anxiety) and group variables (CBT versus wait list; PDT versus wait list). Chi-squared tests will be applied for dichotomous data (MINI). Additionally, random effects models for repeated measures will be used. Multiple regression analyses will be applied to test moderators of change that is to show whether each of the interventions is more effective for some groups of patients (interventions, diagnoses, combination of diagnoses and baseline measurements as predictors). Multiple regression analyses will be also applied to search for mediators of change that are theory-specific (for example, changes in beliefs for CBT and changes in defense mechanisms for psychodynamic therapy). We will take into account to what extent the patients were exposed to the intervention by analyzing the dose-effect relationship.

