## Methods/Design

### Study design

This study is an RCT in which participants will be allocated to one of three conditions: 1) psychodynamic group therapy; 2) cognitive-behavioral group therapy; or 3) the wait-list control group (WL). Participants allocated to the wait list will commence treatment after a 12-week waiting period. The total duration of the study will be three years. Figure 1 shows the trial design. The study protocol, information brochure, and informed consent were approved by the Medical Ethics Committee of Warsaw Medical University (reference number: KB/61/2010).

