The inclusion and exclusion criteria are listed in Table 1. The number of excluded patients and the reasons for exclusion will be recorded. The diagnostic criteria are based on the DSM-V system. Initial assessment will be conducted with independent researchers who will not be involved in the further interventions. It will include a pharmacological consultation by a psychiatrist, personality diagnosis with SCID-II [24, 25], and diagnosis of clinical disorders with the Mini International Neuropsychiatric Interview 5^1^ (MINI) [71, 51]. Diagnosis and evaluation for treatment will be carried out during ambulatory sessions. The focus of the treatment is on psychotherapy, but medication will be continued or initiated if necessary during the screening procedure at least four weeks before the beginning of group psychotherapy (stable medical treatments with selective serotonin re-uptake inhibitors or serotonin-norepinephrine reuptake inhibitors, without dose changes during psychotherapy unless necessary). Baseline measurements and final adjustments of pharmacological treatment will be conducted one day before the beginning of therapy. Randomization will take place during the last diagnostic session. Participants will be randomized using random number tables. A recruitment flow chart is presented in Fig. 1. Patients are planned to be enrolled in the study for over a period of three years. Before participating in the study, each patient will be provided with written information about the study and will be invited to give written consent for inclusion. Participants who do not meet the inclusion criteria will be offered suitable alternative treatment options.

**Table 1 Tab1:** Inclusion and exclusion criteria

Inclusion criteria	Current diagnosis of Axis I anxiety disorder (based on the MINI)
	Diagnosis of comorbid personality disorder (based on the SCID II) or depressive disorder (based on the MINI)
	Aged 18 to 65-years-old
	Sufficient knowledge of the Polish language
	Written informed consent from the patient
Exclusion criteria	Organic brain disorder
	Acute substance-related disorders
	Schizophrenia or bipolar affective disorder
	Severe depression (defined as over 26 points on the Beck Questionnaire)
	Cluster A personality disorders
	Current suicidal ideation and a high risk of suicide
	Restricted intellectual capacity
	Serious unstable medical problems or complications
	Concurrent psychotherapeutic treatment

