### Interventions

Interventions will be offered in a daily unit setting, which is a part of the Wola Center for Mental Health at the district Wola Hospital in Warsaw. Psychodynamic and cognitive-behavioral group psychotherapy has been provided at the Wola Center since 2011. This method was developed by the current team during the last ten years in another clinical setting. When the research project starts, each group therapy will be conducted by two therapists trained in accredited cognitive-behavioral or psychodynamic/psychoanalytic therapy programs.

As is stated in the informed consent, patients will be encouraged not to commence any other therapy in the six-month period after the treatment. In cases of acute deterioration, crisis intervention will be offered. Due to ethical reasons we decided not to ask for postponing other therapy when it seems to be needed. Further treatment choices of the patients will not be controlled.

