Treatment will start in the morning hours and end in the afternoon. According to the Polish health care regulations, patients treated in a day hospital setting should have a therapeutic program for at least five hours a day. This study will be conducted in closed-ended groups. The hospital will provide a small meal during the 45-minute break between the two 90-minute psychotherapy sessions. The acceptable limit of absences is five days throughout the whole treatment. Psychotherapists will receive weekly supervision by certified supervisors. All spoken psychotherapy sessions will be recorded, and a random selection of 10 % from each therapy will be analyzed by two different independent raters on protocol adherence. This will ensure that the essential ingredients are being covered by the therapist and, if not, then the reason for the deviation will be recorded. The reported deviation will be considered minor or major by the principal investigator, who will decide if the particular group should be excluded from the study. The Comparative Psychotherapy Process Scale (CPPS) [34] will be used for this purpose, together with *ad-hoc* checklists based on specific group treatment manuals. The CPPS is designed to assess the distinctive features of psychodynamic-interpersonal and cognitive-behavioral treatments.

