The main therapeutic factors are: 1) mirroring, namely that patients can recognize their own aspects in the fantasies, behaviors, and problems of other group members; 2) sharing, namely that patients share information, which helps them to understand themselves, their interactions with others, and their own problems; and 3) condenser phenomena, namely that unconscious material is easily expressed through the common influence of group members on one another. Shared associations help to understand the symbolic significance of experiences. Additionally, universal group factors are taken into account [87]. The therapists use techniques of clarification, confrontation, and interpretation. As in other psychodynamic short-term therapies, this approach is more structured. To intensify the therapeutic processes, three additional techniques are used: 1) memoir, namely that each patient describes his or her own life story, which consists of important emotional experiences, and reads it during one therapeutic session; 2) elements of role playing and/or psychodrama, namely that the patient presents his or her way of talking to important persons; 3) a summary, namely that patients receive written structured feedback from other patients in the final stage of therapy.

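### Therapy is delivered in closed groups, but the lead analyses and sample size treat patients as independent; if outcomes within a group are correlated, standard errors are too small

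*Protocol article*

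**What the plan says.** On delivery, the protocol states "This study will be conducted in closed-ended groups" and "each group therapy will be conducted by two therapists trained in accredited cognitive-behavioral or psychodynamic/psychoanalytic therapy programs". The psychodynamic section lists among its therapeutic factors that "unconscious material is easily expressed through the common influence of group members on one another", and the cognitive-behavioral section says that its group format makes use of cohesion among members. The principal investigator may also exclude a whole therapy group after a deviation from the manual.

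Allocation is by patient: "Participants will be randomized using random number tables". The control arm has no therapy group while it waits: "Participants allocated to the wait list will commence treatment after a 12-week waiting period".

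On analysis, the Statistical analysis section says "Analyses of variance with repeated measures (three measurement points: pre, post, and follow-up) will be applied for continuous data". It assigns chi-squared tests to the MINI outcome. The primary planned comparison is the time-by-arm interaction for each therapy against the wait list. As an addition, "random effects models for repeated measures will be used". No sentence names therapy group or therapist as a level.

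The Sample size calculation section uses effect sizes, an alpha of 0.05, power of 0.80 and 25 % dropout. It gives no ICC, therapy-group size or design effect. The limitations in the Discussion do not mention clustering.

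**The concern.** Patients who share a room, two therapists and each other's company for 12 weeks will tend to have outcomes more alike than patients in different groups. The protocol counts on this, since it lists mutual influence as a mechanism. Repeated-measures ANOVA and the chi-squared test both take patients as independent. With positive correlation within groups, an arm mean carries less information than its patient count suggests, and the computed standard error is too small.

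The clustering is in two of the three arms, so the design is partially nested. Each primary contrast with the wait list has one clustered arm and is affected less. The comparison of the two therapies has two clustered arms and is affected more. In that comparison, one or two unusual groups or therapist pairs could be read as a difference between methods.

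**Working it through.** **1. The plan's own sample sizes.** Fixed-effects ANOVA power for independent patients was used: noncentral F with noncentrality f² × N, alpha 0.05, power 0.80.

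| Target | Stated (2 × 3 / 3 × 2) | Recomputed |
|---|---|---|
| f = 0.29 | 96 / 120 | 96 / 120 |
| effect size 0.24, taken as f | 140 / 171 | 140 / 171 |
| interaction, f = 0.25 | 156 / 159 | 158 / 158 to 159 |

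The total is 159 × 1.25 = 198.75, rounded up to 199. All of the inflation is for dropout and none is for clustering.

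**2. Assumptions.** The protocol gives neither figure below, so both are ranges.
- ICC of the pre-to-post change within a therapy group: 0.02 to 0.10.
- Analysed patients per therapy group, m: 6 to 10. The low end allows for dropout: 8 × 0.75 = 6.

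Arms are taken as equal in size.

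**3. Formulas.** The design effect is DE = 1 + (m − 1) × ICC. The ratio of the true to the computed standard error is:
- therapy versus wait list (one clustered arm): √((DE + 1)/2);
- therapy versus therapy (two clustered arms): √DE.

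The true type I error at nominal 0.05 is 2 × (1 − Φ(1.96 / ratio)).

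Example with m = 10 and ICC 0.05: DE = 1 + 9 × 0.05 = 1.45. Against the wait list, √(2.45/2) = 1.107, giving 0.077. Therapy versus therapy, √1.45 = 1.204, giving 0.104.

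**4. Results.**

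| m | ICC | DE | Type I error, versus wait list | Type I error, therapy versus therapy |
|---|---|---|---|---|
| 6 | 0.02 | 1.10 | 0.056 | 0.062 |
| 6 | 0.05 | 1.25 | 0.065 | 0.080 |
| 6 | 0.10 | 1.50 | 0.080 | 0.110 |
| 8 | 0.02 | 1.14 | 0.058 | 0.066 |
| 8 | 0.05 | 1.35 | 0.071 | 0.092 |
| 8 | 0.10 | 1.70 | 0.092 | 0.133 |
| 10 | 0.02 | 1.18 | 0.061 | 0.071 |
| 10 | 0.05 | 1.45 | 0.077 | 0.104 |
| 10 | 0.10 | 1.90 | 0.104 | 0.155 |

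Simulation of an unclustered t-test on change (20,000 runs per cell, 64 to 70 patients per arm) agrees. At m = 8 it gave 0.059, 0.068 and 0.091 against the wait list, and 0.065, 0.092 and 0.132 for therapy versus therapy, at ICC 0.02, 0.05 and 0.10. At m = 10 it gave 0.059, 0.077 and 0.104, and 0.071, 0.102 and 0.158. At ICC = 0 it gave 0.048 to 0.050. The m = 6 rows rest on the formula alone.

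**5. Power.** Apply DE to the two therapy arms only, so that N becomes N × (2 × DE + 1)/3. Completers are 199 × 0.75 = 149.
- Wait-list target of 120 (f = 0.29, 3 × 2). ICC 0.05: 120 × 3.70/3 = 148 (m = 8) and 120 × 3.90/3 = 156 (m = 10). ICC 0.10: 176 and 192.
- Interaction target of 159 (f = 0.25, 3 × 2). ICC 0.05: 159 × 3.70/3 = 197 and 159 × 3.90/3 = 207.

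The wait-list main-effect target is therefore roughly met at ICC 0.05 and missed at 0.10. The interaction target, computed the plan's way, is missed at both. However, the plan's sizes reproduce only without within-patient correlation. With a correlation of 0.5 (an assumption), the same interaction needs only 28 (2 × 3) or 42 (3 × 2) patients.

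**The case against.** The best reply has four parts.

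- **The inflation is conditional.** It needs a positive ICC, and the protocol gives neither an ICC nor a group size. This stands. A reader might infer that false positives certainly exceed 5%. The protocol does not establish that, and at ICC 0.02 the excess on the primary contrasts is about one percentage point or less.
- **The largest figures belong to a secondary question.** The primary planned comparison is each therapy against the wait list, and the sample size section calls the comparison of the two therapies additional. This also stands, so the wait-list figures should lead. The comparison between therapies is still a listed objective.
- **The random-effects models might include therapy group.** The protocol does not list their random effects, and model levels are often left to the analysis plan. One cannot say that therapy group is excluded. But these models are additional, are described only as for repeated measures, and do not alter the lead ANOVA, the chi-squared tests or the sample size.
- **A power shortfall is not shown.** A reader might infer that the trial is underpowered. A t-test with 50 per arm and d = 0.58 does fall from 0.82 to about 0.74 to 0.76 at ICC 0.05, but neither that test nor the 0.82 is in the plan. As shown above, the wait-list main-effect target is roughly met at that ICC, and within-patient correlation could more than offset the loss for the interaction. What stands is narrower: the stated 0.80 contains no allowance for clustering.

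**Conclusion.** The point holds in conditional form. The protocol describes correlated patients and fixes lead analyses and a sample size for independent ones. Because the main tests and the full sample size calculation are stated, this is more than a detail deferred to an analysis plan.

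If the within-group ICC is positive, the planned standard errors are too small. Under ICC 0.02 to 0.10 and 6 to 10 analysed patients per group, type I error at nominal 0.05 is about 0.06 to 0.10 for the primary wait-list contrasts and about 0.06 to 0.16 for therapy versus therapy. Confidence is high in the omission and lower in its size, which rests wholly on those assumptions.

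The stated power of 0.80 holds only at ICC = 0 under the plan's own method. The net loss depends on the ICC, the group size and the within-patient correlation, none of which is given.

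**What to change.** - **Lead analysis.** Use a partially nested mixed model: a random therapy-group effect in the two therapy arms only, each wait-list patient as a cluster of one, and Satterthwaite or Kenward-Roger degrees of freedom.
- **Identifiers.** Record therapy group and therapist pair for every patient from the start of enrolment. If a pair leads more than one group, add a pair effect or a sensitivity analysis for it, because a group effect alone does not absorb pair effects. The imputation model should respect the same grouping.
- **MINI outcome.** Replace the plain chi-squared test with a cluster-adjusted analysis that has a small-sample correction. About 50 completers per arm (149/3) in groups of 6 to 10 means roughly 5 to 8 groups per therapy arm, which makes a mixed logistic model fragile.
- **Power.** Restate it over a stated range of ICC and group size, without enlarging the trial.

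The cost is revised analysis wording, two database fields, wider intervals and a lower stated power. The article gives recruitment as still to begin, so the identifiers can be collected prospectively.

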### Assessments

Patients are subjected to four assessments: 1) at the screening; 2) at baseline after randomization; 3) at the end of the 12-week treatment; and 4) six months after the end of therapy in order to evaluate the longer-term effects of the treatments. Patients in the wait-list group will have one additional assessment at the end of the 12-week waiting period.

Information from the screening will be used to perform stratified randomization and to validate the inclusion and exclusion criteria. Patients will be assessed by independent and trained clinicians who will remain blind to the treatment conditions, and who will not be involved in direct clinical care of any of the patients. Primary outcome measures and secondary outcome measures can be distinguished in this study. The primary outcome measures include self-report symptoms of anxiety, observer-rated symptoms of anxiety, global improvement, and dichotomized diagnosis of anxiety disorder (improved or unimproved). The secondary outcome measures include personality, depression, self-esteem, defense mechanisms, beliefs about self and others, interpersonal problems, object relations, parental bonding, meta-cognition, and quality of life. The following sociodemographic data will be collected: sex, age, marital status, education, past treatments, symptom history, and medication. We will also examine patients’ expectancy toward change and treatment. Some of the variables, such as the presence or absence of a personality disorder, will be treated in exploratory analyses as predictors and moderators of treatment response. The time points of assessment and measures are presented in Table 3.

**Table 3 Tab3:** Instruments at different assessment points

Instrument	Screening	Baseline	End of Treatment	6-Month Follow-up
STAI		X	X	X
HAM-A		X	X	X
CGI-S		X	X	X
CGI-I		X	X	X
M.I.N.I.	X		X	X
SCID-II	X			
BDI-II	X		X	X
OQ-45		X	X	X
SES		X	X	X
DSQ-40		X	X	X
PBQ		X	X	X
IIP		X	X	X
DWM-S		X	X	X
ECR		X	X	X
BORRTI		X	X	X
MCQ		X	X	X
SWLS		X	X	X
CEQ		X		

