### Instruments

#### Primary measures

The following instruments will be used:State-Trait Anxiety Inventory (STAI) [72, 86]. The STAI measures a person’s situational (or state) anxiety, as well as the amount of anxiety a person generally feels most of the time (trait). The two self-report scales contain 20 items each.Hamilton Anxiety Rating Scale (HAM-A) [33]. The HAM-A is an interviewer-administered and rated measure of the severity of anxiety symptoms. The scale consists of 14 items, each defined by a series of symptoms, and measures both psychic anxiety (mental agitation and psychological distress) and somatic anxiety (physical complaints related to anxiety).Clinical Global Impression - Severity scale (CGI-S) [32]. The CGI-S is a seven-point scale which requires that the clinician rate the severity of the patient’s illness at the time of assessment, relative to the clinician’s past experience with patients who have the same diagnosis.Clinical Global Impression - Improvement scale (CGI-I) [32]. The CGI-I is a seven-point scale which requires that the clinician assess how much the patient’s illness has improved or worsened, relative to a baseline state at the beginning of the intervention.Mini-International Neuropsychiatric Interview 5 (MINI) [51, 71]. The MINI is a short diagnostic interview based on the DSM-IV criteria, which focus on the existence of current psychiatric disorders. It consists of separate modules to diagnose specific disorders.

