The effects of the intervention on symptoms of anxiety are the primary outcome measures in our study. Although the study’s general aim is to compare both treatments with the wait list, an additional comparison has been planned of both treatments on the outcomes. Comparison between all three groups is possible for two subsequent measurements. Due to ethical reasons, subjects from the wait list will start therapy soon after the second measurements and will not be available to participate in the study during the third measurement. As a result, that data will be analyzed in a 3 × 2 experimental plan (three groups available for two repeated measures) and in a 2 × 3 experimental plan (two groups available for three repeated measures). Based on the trials mentioned above, we assumed that we would be able to show the differences between the interventions and the control conditions with a standardized effect size of 0.58 (the lowest value effect size presented in the literature) for continuous outcomes. As this effect size was Cohen’s d suited for t-test comparisons, we conducted a conversion into f suited for analysis of variance (f = 0.29). The sample size was calculated using the G*power software program [23]. Assuming an alpha of 0.05, with a power (1-β) of 0.80, a minimum number of 96 patients is required for a 2 × 3 experimental plan, and a minimum number of 120 patients is required for a 3 × 2 experimental plan. Furthermore, for the purpose of being able to identify the difference between the two treatments, we followed the design of the most similar study [2] and assumed effect sizes of 0.24 for continuous outcomes, which leads to a total sample size of 171 participants for a 3 × 2 experimental plan and a total sample size of 140 participants for a 2 × 3 experimental plan. We will also test possible within-between group interaction, however its effect size is not available in literature. We assumed a medium effect size for the interaction (f = 0.25), which needs 156 participants in a 2 × 3 plan and 159 participants in a 3 × 2 plan. Assuming that there is a dropout rate of 25 %, this means that 199 participants will need to be recruited.

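### CGI-I rates change since baseline, yet it is scheduled at baseline and analysed as a pre/post/follow-up measure, so its baseline value is undefined

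*Protocol article*

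**What the plan says.** Three places in the protocol article bear on this point.

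- **Primary measures** describes the CGI-I as a seven-point clinician rating of how far the illness has "improved or worsened, relative to a baseline state at the beginning of the intervention". CGI-S, listed just before it, rates severity at the time of assessment.
- **Assessments, Table 3** ("Instruments at different assessment points") marks CGI-I at baseline, end of treatment and six-month follow-up. The pattern is the same as for CGI-S, and neither is marked at screening.
- **Statistical analysis** states: "Analyses of variance with repeated measures (three measurement points: pre, post, and follow-up) will be applied for continuous data". Its list of variables reads "primary outcomes: STAI, HAM-A, CGI-S, and CGI-I; secondary outcomes", so CGI-I is a primary outcome handled as continuous in that model. The same section adds: "Primary planned comparison is the interaction between the time (pre-to-post and post-to-follow-up change on anxiety) and group variables", the groups being each therapy against the wait list.

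The article gives no meaning for a baseline CGI-I value and no other analysis for CGI-I.

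**The concern.** The definition makes CGI-I a change score whose reference is the start of the intervention. At baseline no change has yet happened, so there is nothing to rate. The schedule and the model both require a value there all the same. Because Table 3 and the analysis section agree with each other, a stray mark in the table does not explain it.

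Global improvement is a named primary outcome, and its pre-to-post contrast depends on a number that the article does not define. An assessor could enter no change for everyone, could rate change over some period of the assessor's own choosing, or could leave the item blank. The three choices lead to different analyses.

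The reference point raises a second question. When wait-list patients are assessed at 12 weeks they have not begun the intervention, so the definition, read literally, gives their rating no starting point. That rating enters both comparisons with the wait list.

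**Working it through.** **Inputs.** From the article: the CGI-I definition, its schedule, the ANOVA at three time points, the layout described as "3 × 2 experimental plan (three groups available for two repeated measures" with its 2 × 3 counterpart, and the test level ("Assuming an alpha of 0.05, with a power (1-β) of 0.80"). Assumed, because the article gives no CGI-I data: rating SD 1.1, end-of-treatment means 3.6 (wait list), 3.0 and 3.0 (therapies), 50 patients per arm, ratings rounded and limited to 1–7, and 4,000 simulated trials.

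**The plan's own figures.** The point disputes no stated number. For the interaction at f = 0.25, a noncentral F with λ = N·f², df1 = (k − 1)(m − 1) and df2 = (N − k)(m − 1), for k groups and m occasions, gives N = 156 (2 × 3) and N = 159 (3 × 2), as the article states.

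**Case 1: every baseline set to 4, no change.** With two occasions, the time-by-group interaction is a one-way ANOVA on D = post − baseline. If baseline is the constant 4, D = post − 4. The constant cancels from every group difference and every residual, so the interaction F equals the one-way F on the post rating. One simulated data set gave F = 7.781, p = 0.0006 by both routes. Over repeated trials, type I error was 0.053 and power 0.77 by both.

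For the 2 × 3 plan (70 per therapy arm, constant baseline, assumed post/follow-up correlation 0.4 to 0.8, no arm difference), type I error was 0.050 to 0.055 uncorrected and 0.047 to 0.053 with the Greenhouse-Geisser correction (mean epsilon 0.86 to 0.98).

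**Case 2: baseline rated freely.** Let s be the ratio of baseline SD to post SD, and r their correlation. Then

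Var(D) / Var(post) = 1 + s² − 2rs.

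With equal variances (s = 1) this is 2(1 − r): 1.4 at r = 0.3, 1.0 at r = 0.5, and below 1 above that. In general the change score is noisier than the post rating alone whenever r < s/2.

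The simulation drew baseline independently of post (r = 0), centred on 4:

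| Baseline SD (assumed) | Variance ratio before rounding | Power, interaction | Power, post only | Type I error, interaction |
|---|---|---|---|---|
| 0 (constant) | 1.00 | 0.77 | 0.77 | 0.053 |
| 0.5 | 1 + 0.25/1.21 = 1.21 | 0.68 | 0.78 | 0.052 |
| 1.0 | 1 + 1.00/1.21 = 1.83 | 0.49 | 0.78 | 0.047 |

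**Case 3: baseline left blank.** A repeated-measures ANOVA drops a patient who lacks one occasion. If every baseline is blank, no patient is left. Multiple imputation, which the Statistical analysis section allows where appropriate, would be filling in a quantity that has no true value.

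**The case against.** The strongest reply is that the inconsistency does no harm. No change is the natural entry at baseline, and Case 1 shows that the planned test is then exactly the comparison one would want. CGI-S is also primary and has a proper baseline. The primary planned comparison is worded for change on anxiety, so it may not cover CGI-I at all. Baseline is taken after randomization and is an obvious common reference for all arms.

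Much of this stands. It rules out three stronger readings that a reader might infer.

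- *That the CGI-I test is meaningless or invalid.* It is not. Case 1 gives an exact equivalence, Case 2 keeps type I error near 0.05, and the post-to-follow-up contrast can still be read as further change.
- *That a constant first column breaks the variance assumptions.* With two occasions sphericity holds automatically. In the 2 × 3 plan, error rates stayed close to 0.05 in simulation.
- *That medication started during screening would bias the therapy effect through the baseline rating.* The recruitment section places such initiation at least four weeks before therapy and randomization in the last diagnostic session. Medication started before randomization is balanced across arms in expectation, so a rating that reflects it mainly adds noise. That assessors would rate change since screening is also conjecture.

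What the reply does not remove is that the harmless case depends on a convention the article never states, while Table 3 schedules an actual rating. The ambiguity over anxiety does not take CGI-I out of the ANOVA list. The obvious wait-list reference is still not the one the definition names.

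**Conclusion.** Wrong as written. The CGI-I schedule and analysis contradict the article's own definition of the scale, and this goes beyond detail left to a fuller document, because the article fixes both.

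The size depends on what is recorded at baseline. There is no loss if no change is entered for everyone. If it is rated freely, power usually falls, from about 0.78 to 0.68 or 0.49 with assumed baseline SDs of 0.5 and 1.0 and no correlation with the post rating. The loss shrinks as that correlation rises and vanishes at r = 0.5 when variances are equal. If the item is left blank, patients are lost or an undefined value is imputed. The power figures rest on assumed means and SDs. The Case 1 equivalence rests on none.

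The point touches one of four continuous primary outcomes. Whether it reaches the primary planned comparison is unclear from the wording. The missing wait-list reference at 12 weeks is a smaller, related gap that would remain even if the baseline rating were dropped.

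**What to change.** 1. Delete the CGI-I mark from the baseline column of Table 3, and take CGI-I out of the pre-post ANOVA.
2. Compare CGI-I between the three arms at the end of treatment or waiting, for example with baseline CGI-S as covariate, and between the two therapies at follow-up.
3. State that CGI-I is rated against the post-randomization baseline in all three arms, including the wait list at 12 weeks.
4. Keep CGI-S as the global measure in the pre-post model.

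The cost is one table cell and a sentence or two of text, with one rating fewer per patient. No extra patients or staff are needed, and the sample size is unchanged. The Trial status section places the start of recruitment after publication, so on that timetable the change could be made before any data exist.
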